### Overview of PMC intervention

As part of a Unitaid funded project – the Plus Project – Cameroon and Côte d’Ivoire National Malaria Programmes (NMPs) opted to join a process of designing, implementing, and evaluating a pilot PMC project. Other evaluations taking place concurrently, but not reported here, include a cost effectiveness analysis, drug resistance monitoring, a process evaluation, and policy adoption. Briefly, in both countries, the interventions were developed through a co-design process involving key stakeholders, including malaria and vaccination programmes, local leaders and other community representatives, that decided on the number of PMC doses and when to administer them as part of routine health services, as well as and the geographic areas for implementation [11]. The intervention was restricted to the use of SP, with a maximum of eight doses over the first two years of life. Delivery channels and timings of doses were under the control of country stakeholders.

Cameroon decided on an eight-dose PMC schedule whereas Côte d’Ivoire opted for a five-dose approach, both leveraging visits in the current Essential Programme of Immunization (EPI) and Vitamin A delivery schedule. The standard of care in Cameroon and Côte d’Ivoire is five and zero SP doses, respectively (Fig. 1). SP will be delivered at health facilities using EPI infrastructure, by community health workers (CHWs), and actively targeting populations where vaccination coverage is low. All PMC will be delivered by the Ministry of Health (MoH) in each country and will prioritize areas (i) with the highest malaria incidence and (ii) where other chemoprevention-based interventions are not implemented. Eligibility for children to receive PMC will be assessed by the MoH staff at the point of SP administration. PMC eligibility includes being the correct age to receive each dose scheduled in concordance with the EPI schedule, not having received SP within the previous four weeks, no known allergies to SP, or not concurrently taking any contraindicated medication according to manufacturer’s guidelines. All children will be eligible to receive PMC irrespective of whether they participate in the study activities.

**Fig. 1 Fig1:**
[figure not shown]
Title: Perennial malaria chemoprevention (PMC) dose schedule in intervention and areas receiving standard of care as integrated within the existing essential programme on immunization (EPI) delivery schedule Legend: Perennial malaria chemoprevention (PMC) delivery schedules in Cameroon and Côte d’Ivoire denoted by black checkmarks with the Plus Project activities denoted in orange and any doses of PMC as part of standard of care shown in orange alongside vaccination visits and ideal child age as part of the Essential Programme on Immunization (EPI) and the standard of care outlined in national guidelines. Note: Penta 2 and penta 3 refer to the 2nd and 3rd dose of the pentavalent vaccine providing protection against diphtheria, pertussis, tetanus, hepatitis B and haemophilus influenza B. Vit A refers to when doses of vitamin A are scheduled. MR1 and MR2 refers to vaccination against measles and rubella

### Aims and objectives

This is a multi-site study with the primary aim to evaluate the impact of routine delivery of PMC on malaria incidence during the first two years of life. In Cameroon we will compare the effect of up to eight versus the standard of care of five doses, whilst in Côte d’Ivoire we will compare the effect of five versus zero SP doses, as the standard of care. Secondary objectives include determining any differences in: (i) severe malaria, malarial deaths, anaemia, and severe anaemia; (ii) differences in all indicators by country, delivery platform and the number and timing of doses; and (iii) any dose response effect or differences according to distance to the health facilities, as a proxy for access to care.

Evaluation of malaria interventions requires knowledge of the regional epidemiology of malaria and active and passive surveillance methods have been proposed for malaria vaccine efficacy studies. Passive case detection methods are limited to those seeking health care and are likely to underestimate burden of malaria in the community but may provide information on the clinical presentation and management of malaria relevant for planning health services. In contrast, active surveillance methods can minimise the effect of health care-seeking behaviour on malaria detection and measures of effect. It also allows for understanding the age, spatial and temporal patterns of disease in community settings. To address these issues, we will employ two approaches to address the study objectives. First, we will develop a passive cohort, which will capture routinely collected health data as part of all child visits to participating health facilities in the selected study sites. Secondly, we will form and prospectively follow an active cohort of children who will be visited at their households every three months over the study period. Reported malaria and anaemia cases in children under 5 years from the 5 years prior to the start of the study will also be collected to ensure results can be interpreted within the context of the broader malaria transmission patterns at each site.

## Methods

### Study site

Areas with the highest malaria transmission in both Cameroon and Côte d’Ivoire were purposively selected to be PMC implementation areas to maximize any observable impact of the intervention. Control areas in both countries were also identified that had epidemiological profiles that were similar to the intervention areas. In Cameroon, we chose Soa and Mbankomo in the Central Region as the intervention and the control areas, respectively, whilst in Côte d’Ivoire, Séguéla and Kani in the Worodougou Region were chosen as the intervention and control areas, respectively. These sites were chosen based on the size of the population, number of EPI facilities, malaria incidence, EPI coverage, and availability of a suitable control population receiving standard of care (Fig. 2).

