### Study design

All health facilities providing EPI services in selected study sites and corresponding catchment populations will be eligible for inclusion and constitute the primary sampling unit for this evaluation. Health facilities will be randomly selected for inclusion (Fig. 3). All non-EPI/PMC facilities within the selected EPI catchment areas, will be included in the passive cohort data collection, described below (Table 1). In the selected EPI facility catchment areas, several study activities will be conducted: (i) a census to enumerate all households, primary caregivers and children under 36 to characterize the population eligible to receive PMC (0–24 months) as well as when they age out of the intervention (25–36 months), (ii) a passive cohort at health facilities to monitor clinical episodes of malaria and anaemia as well as receipt of EPI vaccinations and PMC in children under 36 months, and (iii) to monitor malaria and anaemia in a subgroup of participating children in an active cohort over an 18-month period. The same procedures will be employed in both intervention and control areas in Cameroon and Côte d’Ivoire.

**Table 1 Tab1:** Eligibility criteria for each study component in the PMC impact evaluation study

	Inclusion Criteria	Exclusion Criteria
**Health Facilities**	- Located within the target study sites - Administer EPI/PMC services	- Located outside of the target study area
**Census - Household**	- Located within the catchment area of selected health facilities - Head of household provides consent	- Located outside of the selected health facility catchment area - Head of household not present or refuses participation
**Passive Cohort - Child**	- Regularly resides in households included in the census - Age 36 months or less at time of census - Primary caregiver provides informed consent	- Head of household refused participation in the census - Primary caregiver not present or refuses participation - Not expected to reside in the selected household for the study duration - Age greater than 36 months of age at recruitment visit

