### Passive cohort

All children up to 36 months of age residing in enumerated households during the census will be eligible for inclusion in the passive cohort and enrolled upon provision of written informed consent from their primary caregiver (Table 1). Enrolled children will be passively monitored to record both EPI vaccinations and PMC visits as well as clinical visits for malaria and anaemia to the health facility and/or CHWs over the 18-month study period. Older children (24 to 36 months at baseline) are not eligible to receive the intervention but will be enrolled in this study activity for two reasons: first, the older children will serve as an internal control as it is assumed that they will experience a similar malaria transmission intensity but will not receive the intervention and, secondly, as children will be followed for 18 months information will be available on children who age-out of eligibility to assess any impact beyond when children are eligible to receive PMC. Children will not be censored according to age.

During the passive cohort recruitment, trained fieldworkers will record basic demographic information about the child, recent malaria cases, amongst other information. An anonymous and unique QR code with the participant ID linked will be attached to each child’s health and vaccination record books. This QR code will be used to identify children participating in the study when they interact with the health system and facilitate linking the data generated by the routine system on EPI, PMC or clinical visit, which are stored in separate registers, with the research activities. During recruitment, the national health ID number assigned to each child and written in the health and/or vaccination record books will be recorded. The names of children and primary caregivers will also be recorded to provide a means to verify that children present match ID numbers. This also serves as a back-up method to link health information data that is routinely collected in different registers. Caregivers will be encouraged to take children to the participating facilities or CHWs to receive EPI vaccinations or PMC or for any illnesses.

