Study staff will be present during the scheduled EPI visits to record when children received each dose of PMC. This may occur at health facilities or during active campaigns initiated by the health facility staff where vaccinations, including the newly introduced RTS, S vaccine where present, Vitamin A or SP is distributed. Data collected will include the child’s ID number, the date, location, and which health interventions were administered at that contact point. Where CHWs administer some of the SP or Vitamin A doses, they will record the data for the relevant contact point. The study staff will also collect, information on all clinical malaria and anaemia episodes throughout the 18-month study period. When a child participating in the passive cohort (i.e., has a QR code in their record book or the caregiver makes their participation known and confirmed through looking up their name) visits a study health facility or CHW, information about their visit will be recorded including date, diagnosis and treatment received and whether a referral was made. For children receiving inpatient treatment for anaemia or malaria, additional information including clinical symptoms and details of any complications, treatments received, the outcome, and date of discharge will be collected. Data will also be collected on any children who die in hospital during the study period. All data will be obtained from the clinical registries and confirmed by the facility staff.

Finally, to ensure that results are interpreted within the context of the broader trends in malaria transmission and the incidence of anaemia, routine surveillance data for each health facility will be collected up to five years before the start of the evaluation untill the end of the study. Data will consist of monthly aggregated data per health facility per 12-monthly age-band for children under 5 years of age. Key variables to be collected include the number of attendees, number of uncomplicated and complicated malaria cases, the number of malaria deaths, the number of anaemia and severe anaemia cases.

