### Data analysis

The primary analysis will be based on intention to treat (ITT), including all children residing in the intervention area as the exposed group. All available data up to the time of censuring (e.g., loss to follow-up, withdrawal, death, or study completion), irrespective of whether the child received any, part, or all the intended PMC doses. An additional per-protocol analysis will be completed which includes children who received at least one dose, all doses, or specific doses of PMC. The period of protection provided by SP is up to one-month post treatment and thus will constitute the protective window of those receiving the intervention. Data for both countries will be combined for analysis as well as assessed separately to ensure context specific nuances are fully assessed.

Incidence rates for malaria and anaemia will be calculated using multivariable Poisson regression, difference-in-difference, and interrupted time-series models comparing intervention and control areas [14–16]. Incidence rates, rate differences, and rate ratios between intervention and control area will be calculated for the ITT and per-protocol analysis. Malaria incidence will be determined by the number of malaria cases confirmed by either RDT or microscopy identified in either the passive or active cohort. Person-time at risk for each study outcome will be calculated based on the date of recruitment into the study population until the date of censuring or study end. For children who leave the study prior to the end date, the date of exit will be the date where they moved, withdrew from the study, or died. If that date is not known, the midpoint between the date of last contact and the date the loss was detected will be used. Protective effectiveness will be calculated for the intervention period including the 18 months of follow-up for the periods where PMC doses differ, stratified by first and second year of life, as well as during the post-intervention period, starting at 24 or 18 months of age in Cameroon and Côte d’Ivoire, respectively, to estimate any potential rebound in malaria.

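### With one area per arm in each country, the 80% power assumes no between-area variance, and the effectiveness conclusion is not tied to the planned before-after contrast

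*Protocol article*

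**What the plan says.** - **Allocation.** Protocol article, Study site: in Cameroon "we chose Soa and Mbankomo in the Central Region as the intervention and the control areas". In Côte d'Ivoire, Séguéla and "Kani in the Worodougou Region were chosen as the intervention and control areas, respectively". The high-transmission areas "were purposively selected to be PMC implementation areas to maximize any observable impact of the intervention", and the control areas were sought for a similar epidemiological profile.
- **Sampling.** Study design: EPI facilities and their catchments "constitute the primary sampling unit for this evaluation", and "Health facilities will be randomly selected for inclusion". This is random selection within areas. PMC is not allocated to facilities.
- **Power.** Sample size: 80% power at the 5% level, a term of 0.25 labelled an intra-cluster correlation, and a 3:1 ratio. This gives 26 and 9 facilities in Cameroon and 14 and 5 in Côte d'Ivoire. No term for areas appears. The Abstract repeats the power claim without conditions.
- **Analysis.** Data analysis: the primary analysis is ITT by area of residence, using "multivariable Poisson regression, difference-in-difference, and interrupted time-series models comparing intervention and control areas", with no order among them. The only correlation named is that between repeated measures on one child.
- **Before-after material.** Passive cohort: "routine surveillance data for each health facility will be collected up to five years before the start of the evaluation", as monthly totals in 12-month age bands. Children aged 24 to 36 months at baseline are also enrolled because "the older children will serve as an internal control".

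**The concern.** PMC is introduced at the level of the area, and each arm of each country has one area. Facilities in the same area share its PMC status and whatever else is particular to that area, so they are not independent allocations. More facilities or children reduce sampling error within an area but say nothing about how far two untreated areas would differ. A comparison of the follow-up period alone leaves zero degrees of freedom for that quantity.

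The areas do differ in ways that bear on case detection. From the Cameroon and Côte d'Ivoire sections:

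- Community health workers are active at 28 of 39 facilities in Soa (72%) and 10 of 32 in Mbankomo (31%).
- They are active at 33 of 42 facilities in Séguéla (79%) and all 8 in Kani.

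The Data analysis section counts confirmed cases from either cohort, so a difference in care-seeking or access can enter the outcome directly. At stake is whether a modest difference between two areas could be reported as PMC effectiveness with more certainty than the design allows.

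**Working it through.** **Inputs.** From Sample size: facilities 26/9 and 14/5; children 1,560/540 and 1,148/410, that is 60 and 82 per facility; 20% loss; 18 months; rate ratios 0.70 and 0.60; between-cluster term k = 0.25. From the country sections: 2020 incidence of 0.597 and 0.572 per child-year. Two assumptions are mine: these incidences are the planning rates, and the test is two-sided.

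**Step 1: reproduce the plan's counts.** Cluster formula for rates with 3:1 allocation, λ0 and λ1 the control and intervention rates, y the person-years per facility:

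control facilities = (1.96 + 0.84)² × [(λ0/y + k²λ0²) + (λ1/y + k²λ1²)/3] / (λ0 − λ1)²

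- Cameroon: y = 60 × 0.8 × 1.5 = 72; λ1 = 0.418. Then 7.849 × (0.03057 + 0.01672/3) / 0.1791² = 8.84 control and 26.5 intervention facilities (8.74 and 26.2 if loss is taken as n/1.2). Stated: 9 and 26. Power at 26/9 is 80.5%.
- Côte d'Ivoire: y = 82 × 0.8 × 1.5 = 98.4; λ1 = 0.343. Then 7.849 × (0.02626 + 0.01085/3) / 0.2288² = 4.48 and 13.4. Stated: 5 and 14. Power at 14/5 is 83.8%.

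A literal ICC of 0.25, with design effects of 12.75 and 17.15 applied to a comparison of proportions, gives about 22 and 65 facilities in Cameroon and 13 and 38 in Côte d'Ivoire. Of the readings tried, only 0.25 as a coefficient of variation, with facilities independent and area variance zero, recovers the stated figures.

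(Soa is described as having 20 EPI facilities, fewer than the 26 required. That is a separate matter. At 20/9 the power is 78.6%, which does not change this point.)

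**Step 2: add an area term.** Under no effect, the facility-level variance of the log rate ratio is (k² + 1/(yλ0)) × (1/c1 + 1/c0), where c1 and c0 are the facility counts.

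- Cameroon: (0.0625 + 0.0233) × (1/26 + 1/9) = 0.0128; SE 0.113.
- Côte d'Ivoire: (0.0625 + 0.0178) × (1/14 + 1/5) = 0.0218; SE 0.148.

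Let areas vary with SD s in log rate. The true variance is then larger by 2s², and a test that ignores it has type I error 2 × [1 − Φ(1.96 × SE_facility / SE_total)]. For Cameroon at s = 0.10: SE_total = √(0.0128 + 0.02) = 0.181; 1.96 × 0.113/0.181 = 1.23; error 22%.

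| Assumed s | Cameroon | Côte d'Ivoire |
|---|---|---|
| 0 | 5% | 5% |
| 0.05 | 10% | 8% |
| 0.10 | 22% | 16% |
| 0.20 | 47% | 36% |

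**Step 3: power if the area variance were known and included.** On the rate scale, add s²(λ0² + λ1²) to the variance, with s now as a coefficient of variation. At s = 0.10:

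- Cameroon: variance 0.00404 + 0.00531 = 0.00935; 0.1791/0.0967 − 1.96 = −0.11; power 46%.
- Côte d'Ivoire: variance 0.00603 + 0.00445 = 0.01048; 0.2288/0.1024 − 1.96 = 0.28; power 61%.

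With unlimited facilities the ceilings at s = 0.10 are 69% and 93%.

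**Step 4: the clustering that the text names.** If an interval carried only Poisson variation, with no facility term, its type I error would be about 31% and 36% at k = 0.25 even with s = 0.

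**The case against.** The case on the other side is substantial.

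- **Controlled before-after work is planned.** Difference-in-difference and interrupted time-series models are listed, up to five years of earlier data are collected, and older children are followed. A reader might infer that this analysis is missing. It is not. What is missing is any requirement that it support the effectiveness conclusion. Ranking models is often left to an analysis plan, so the lack of a ranking alone would not be a finding.
- **Intervals.** A reader might infer that the intervals will treat facilities as replicates, or will ignore facility clustering. The article says neither. It names within-child correlation only, which does not match the clustering used for the sample size.
- **Comparability.** The areas were paired for similarity, 2020 incidence is given as equal within each pair (597 and 572 per 1,000), and covariate and transmission adjustment is planned. This lowers the risk. One shared figure for one year does not show parallel trends, and adjustment reaches only what is measured.
- **Assumed variance.** The documents give no area SD. Treating the paired areas as independent draws may overstate the error, and the percentages apply to a facility-level post-period test, not to difference-in-difference.
- **Difference-in-difference as sole primary estimate.** This would be a real trade. No pre-PMC follow-up of the active cohort is described, yet power rests on that cohort. The earlier data are routine totals that depend on care-seeking. PMC recipients also age into the 25–36-month band, and Cameroon's standard of care already includes five SP doses, so older children there cannot be assumed free of SP.

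These points limit the claim and shape the remedy. They do not supply the missing area term in the power statement.

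**Conclusion.** The point holds in a limited form. The stated 80% power is conditional on no difference between areas beyond facility variation, and the plan states it without that condition. With one area per arm, the post-period rate ratio cannot by itself attribute a difference to PMC, and the plan does not make the conclusion depend on the analyses that would help.

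The size depends on an unknown. An area SD of 0.10 would roughly quadruple the nominal 5% error in Cameroon and triple it in Côte d'Ivoire; at 0.05 the inflation is mild. These figures also rest on 0.25 being a coefficient of variation, which is inferred from the counts because the article calls it an intra-cluster correlation.

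It would go too far to say that a district difference will pass for a PMC effect. The documents show that the design leaves this possible, not that the paired areas differ in underlying malaria incidence.

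**What to change.** 1. **Sample size, and the matching sentence in the Abstract.** State that 80% power holds only if there is no area-level difference beyond facility variation, and that inference is conditional on the two areas in each country.
2. **Data analysis, models.** Include facility-level clustering. Report the controlled before-after contrast on the pre-PMC facility data beside the active-cohort area rate ratio. Attribute a difference to PMC only if the two agree, with the criterion for agreement written down in advance.
3. **Data analysis, placebo periods.** Run the same contrast on the pre-PMC years and report its spread next to the estimate.
4. **Older-age contrast.** Use only children already aged 24–36 months at baseline, not the aggregate 25–36-month bands that PMC recipients enter during follow-up.

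No new sites or data are needed. The costs are a wider interval and a less favourable power statement. The remedy also has limits: the earlier data are routine aggregates that depend on care-seeking, at most five years from one pair of areas per country give only a rough measure of spread, and difference-in-difference removes stable area differences but not area-specific shocks.
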